## ABBREVIATIONS

DALY: Disability Adjusted Life Years

DEET: Di-ethyl-*M*-toluamide

IgM: Immunoglutinin M

IgG: Immunoglutinin G

IRS: Indoor Residual Spraying

ITN: Insecticide Treated Net

JE: Japanese Encephalitis

Lao PDR: Lao People’s Democratic Republic

LLIN: Long Lasting Insecticide Treated Net

LSHTM: London School of Hygiene & Tropical Medicine

NOEL: No Observed Effect Level

PMD: *p*-Methane-3,8-diol (insect repellent from lemon eucalyptus)

PSI: Population Services International (social marketing organisation)

RDT: Rapid Diagnostic Test

*s.l.*: *sensu lato*

*s.s.*: *sensu stricto*

VHV: Village Health Volunteer

WHO: World Health Organization

## PROTOCOL SUMMARY

Population

Approximately 8,000 rural agricultural workers and children aged from 6 to 60 years, resident in 126 villages in Sekong and Attapeu Provinces in southern Lao PDR.

Sites

One

Study Duration

March 2009 to Feb 2012

Subject Participation Duration

Either 7 months from June to December 2009, or 9 months from April to December 2010

Interventions

1. A single Long-lasting insecticide treated net (PermaNet®2.0, deltamethrin 55mg/m2, mesh 25 holes/cm2) for every 1.5 people in the household

2. 15% DEET lotion or a placebo lotion (both supplied by SCJohnson)

Objectives: The aim of the study is to evaluate the efficacy of 15% DEET insect repellent to reduce malaria incidence in rural populations living in southern Lao PDR.

Study Design: The study will take place in Attapeu and Sekong Provinces in southern Lao PDR and will involve 8000 subjects clustered by household. Participants will be primarily recruited amongst rural agricultural populations who often work and sleep away from the village during the wet season. Either a DEET or placebo lotion will be provided for participants to use every evening. All participants will be supplied with long lasting insecticide treated nets (LLINs). Data collection will take place during June to December of 2009 and April to December of 2010. Malaria cases will be identified through active case detection using RDTs (rapid diagnostic tests) at baseline and at monthly intervals post-intervention. Secondary outcomes are all-cause fevers self reported via monthly questionnaires, and dengue, JE and typhus IgM/IgG from bloodspots collected at baseline and exit.

ClinicalTrials.gov Identifier: NCT00938379

## BACKGROUND

### Study Area

Attapeu and Sekong Provinces in south-eastern Lao PDR border both Cambodia to the south and Vietnam to the west. The wet season runs from April to October, followed by a cool dry season November to January and a hot dry season February to March. Rice farming is the main economic activity in these two provinces, 57% and 71% of Attapeu and Sekong’s populations are farmers respectively (UNDP, 2001).

### Malaria in Lao PDR

Malaria is a major public health problem in Lao PDR: the World Health Organization estimates that malaria was responsible for 46 lost DALYs per 100,000 population in 2004 (WHO, 2009). The prevalence of malaria recorded in Lao PDR in 1998 was 55 cases per 1,000 population; but in Attapeu the prevalence was 101 per 1,000 and in Sekong it was 163 per 1,000 the highest rate in the country (UNDP, 2001).

Current policy is for the entire population at risk (estimated to be 70% of the country) to receive insecticide treated nets (WHO, 2005). In addition free diagnosis and ACT (artemisinin combined therapy) treatment has been implemented to poor populations. Artemisine resistance has been recorded in neighbouring Cambodia, although it is not yet recorded in Laos (Singhasivanon *et al.* 2003).

In general the use of DEET (*N,N-*diethyl-*M*-toluamide) repellents by rural people is often low due to cost, but other methods of personal protection such as coils or repellents made from locally available ingredients such as neem oil are still used (Frances and Wirtz, 2005).

### Malaria Vector Behaviour in Lao PDR

The main malaria vectors in Lao PDR are *Anopheles dirus*, *An. minimus*, *An. maculatus* and *An. jeyporiensis* (Toma *et al.* 2002; Vythilingam *et al.* 2003; Vythilingam *et al.* 2005). Feeding time amongst the *An. dirus* complex is observed to vary with sibling species (Baimai *et al.* 1988), in Laos the highest biting frequencies are recorded between 21.00h and 02.00h (Toma *et al.* 2002; Vythilingam *et al.* 2003; Vythilingam *et al.* 2005). No preference for indoor or outdoor feeding has been observed for *An. dirus s.l.* in Lao PDR (Vythilingam *et al.* 2003; Vythilingam *et al.* 2005). An early feeding cycle has been found for *An. minimus* *s.l.* with most biting occurring from 18.00h to midnight (Tun-Lin *et al.* 1995; Rattanarithikul *et al.* 1996; Zhou 2003). Several studies have also found a second peak following this around 01.00h (Chareonviriyaphap *et al.* 2003; Vythilingam *et al.* 2003; Sungvornyothin *et al.* 2006). Most studies have recorded little or no indoor or outdoor feeding preference in *An. minimus s.l.* (Socheath *et al.* 2000; Chareonviriyaphap *et al.* 2003; Tun-Lin *et al.* 2003; Vythilingam *et al.* 2003; Trung *et al.* 2005; Vythilingam *et al.* 2005; Sungvornyothin *et al.* 2006) although a comparison of sibling species found *An. harrisoni* to be more exophagic than *An. minimus s.s.* (Van Bortel *et al.* 1999). Strongly exophagic behaviour is recorded for *An. maculatus s.l.* throughout Southeast Asia (Schultz 1992; Torres *et al.* 1997; Socheath *et al.* 2000; Hassan *et al.* 2001; Vythilingam *et al.* 2003; Trung *et al.* 2005). It also generally feeds early from 18.00h to around 22.00h (Schultz 1992; Rattanarithikul *et al.* 1996; Socheath *et al.* 2000; Vythilingam *et al.* 2003; Zhou 2003). *An. jeyporiensis* shows a high level of behavioural plasticity; recorded feeding predominately indoors in Lao PDR, but mostly outdoors in Vietnam (Vythilingam *et al.* 2003; Trung *et al.* 2005). This is possibly due to the presence of sibling species, or misidentification as *An. jeyporiensis* is very difficult to distinguish morphologically from *An. harrisoni* (Do *et al.* 2008). Similarly, peak biting is recorded between 23.00h and 03.00h in Myanmar (Oo 2003), but from 22.00h to 06.00h in Lao PDR (Vythilingam *et al.* 2003). As biting can start as early as 18.00h and often takes place outdoors, bednets may not provide complete protection from malaria transmission

### Repellent Protection from Biting

Repellent trials have tested concentrations of DEET from 5-75%, in the laboratory and in the field (Table 1), however different mosquito densities and methodologies make comparisons difficult. One particular problem is the proximity of controls and treatments, which if too close can result in diversion of mosquitoes from treated to control, artificially distorting the difference between the catches (Moore *et al.* 2007). However, concentrations of DEET below 15% do not appear to give useful levels of protection.

### Table 1. Design and outcomes of DEET repellency trials against Southeast Asian anophelines

| Trial design | Outcome |
| --- | --- |
| Untreated arm was placed in a cage with 200 *An. dirus* for 1 minute. Then the arm was treated with 5%, 10% or 20% DEET and placed in the cage for 5 minutes. The treated arm was placed in the cage for 5 minutes every 30 minutes following until three bites were recorded, giving the protection time (Frances *et al.* 1996a). | Average protection time was less than 5 minutes for 5% DEET, 7.5 minutes for 10% DEET and 105.5 minutes for 20% DEET. |
| 25% DEET or 100% ethanol control applied to lower legs 1 hour before the start of collections. Outdoor landing catches performed in rubber tree plantation in Thailand for 7 hours starting at 18.00h or 19.00h. *An. dirus* was most common species (Frances *et al.* 1996a) | 25% DEET gave over 80% protection for up to 4 hours, and 50-70% protection for hours 5-7 following application. |
| 33%, 50% and 75% DEET applied to exposed skin and outdoor landing catches performed in forest area in Thailand from 18.00h to midnight. Controls were untreated. *An. dirus* made up 35% of catch, but density was very low (Frances *et al.*  1996b). | 33% DEET gave complete protection for 8 hours as did 75% DEET, although the 50% formulation only protected for 6 hours. |
| 20% DEET and 0.5% permethrin trialled in three different formulations against two controls (70% ethanol and thanaka and water). One treatment applied to arms and legs and pairs with same treatment spaced at least 10m apart. Anophelines in order of biting density; *An. maculatus*, *An. minimus* and *An. dirus*. Landing catches were carried out both indoors and outdoors from 18.00h to midnight, then indoors only until 06.00h, with additional catches outdoors from 05.00h to 07.00h (Lindsay *et al.* 1998). | 98.2-99.6% protection against all mosquitoes. |
| Outdoor catches from 21.00h to 01.00h in non-malarial rural residential area in Malaysia where *Anopheles sinensis* is most abundant species biting humans. 15% DEET in ethanol applied to one side of the body and 12% Bayrepel applied to other, while controls 5m away were untreated (Yap *et al.*  2000). | 15% DEET gave complete protection for 1 hour and 97.5% protection over 8 hours. |
| An arm treated with 20% DEET placed into a cage of 250 *An. dirus* for three minutes every 30 minutes for 12 hours between 18.00h and 06.00h. Protection time defined as time between application and either two bites in a three minute observation period or two consecutive observations with one bite (Thavara *et al.* 2001). | Protection time for 20% DEET against *An. dirus* was 5.8 hours. |
| Volunteers were treated with 20% DEET on one leg and 20% IR3535 on the other. Untreated controls were 1m away. Outdoor landing catches were carried out from 19.00h to 24.00h in four sites across Thailand (Thavara *et al.* 2001). | 20% DEET gave 94-100% protection from *Anopheles* biting for 5 hours. |
| 20% DEET and 0.5% permethrin soap applied to all exposed skin and outdoor landing catches carried out from 19.00h to 05.00h. Anopheline species included *An. nigerrimus* and *An. stephensi* (Rowland *et al.* 2004a). | 100% repellency for 10 hours from both culicine and anopheline biting. |

### Repellent Protection from Malaria

Repellent protection from biting is better demonstrated than protection from vector-borne disease transmission. Challenges to disease targeted repellent trials include the varying effect of repellents on different vector species (or even sibling species) and the acceptability of the repellent formulation used. Some of the earliest trials involved military personnel deployed to endemic areas in the 1940s which showed reductions in scrub typhus and sand fly fever incidence (Gupta and Rutledge, 1994).

In areas of seasonal malaria transmission in Ecuador and Peru, repellent soap (20% DEET and 0.5% permethrin) was distributed to nine communities over four months. *Plasmodium falciparum* was found in 86% of cases in Ecuador, while the predominant species in Peru was *P. vivax*. Another nine communities, paired for population, malaria incidence and access to health care, were controls. At the end of the four months, participants were interviewed to determine if they had experienced malaria during the trial. No significant difference was seen in malaria infection in either the control or intervention groups (Kroeger *et al.* 1997). It was suggested that the lack of effect could have been due to low uptake of the soap, it was estimated that the coverage of continuous soap use was only 50-70%. In addition, field trials showed that activity reduced the efficacy of the repellent formulation. It is also possible that the local vector, *An. albimanus*, is less susceptible to DEET than other anophelines.

Almost 900 pregnant women in a camp for displaced Karen people in Thailand were enrolled into a double-blind repellent trial. They were randomised to either 20% DEET in thanaka (a local plant-based cosmetic) or thanaka. The repellent or placebo was applied every evening for an average of 18 weeks per woman. A 28% reduction in *P. falciparum* was recorded in the intervention group, but this was not significantly different from the 15% reduction in the control group (McGready *et al.* 2001a).

In South Africa 15% DEET was applied twice an evening to ankles and feet of all 850 residents of a small community during a malaria outbreak following a flood. Malaria declined to pre-outbreak levels within four weeks, however without a control group in this case, the contribution of repellent to this decline is impossible to quantify (Durrheim and Govere 2002).

Following social marketing of a repellent soap (20% DEET and 0.5% permethrin) in Afghanistan, a case controlled study was carried out using malaria cases from local clinics. Controls were fever patients at the same clinics who tested negative for malaria. Participants were interviewed about their use of the repellent soap the day before, ten days before and for confounding factors such as ITN use. 96% of infections were from *P. vivax*. The use of repellent 10 days before a fever episode was associated with a 45% reduction in the odds of malaria, although this was not significant possibly due to low sample sizes (Rowland *et al.* 2004a).

The same repellent soap (20% DEET and 0.5% permethrin) was given to 67 households in an Afghan refugee camp in Pakistan. A similar number of households were provided with a placebo lotion. Repellent and placebo use appeared to be high, although this was only measured by a single round of interviews with 20 households. Passive case detection for six months found a 44% reduction in the odds of *P. falciparum* infection, although no effect was found for *P. vivax* (Rowland *et al.* 2004b).

A cluster randomised trial in Bolivia randomised 860 households to either 30% PMD (a repellent derived from lemon eucalyptus, *Eucalyptus maculata citriodon*) or 0.1% clove oil as a control. All participants were also provided with insecticide treated bed nets. *P. falciparum* infections were actively recorded by monthly rapid diagnostic tests, and *P. vivax* episodes were passively detected at local clinics. A per protocol analysis which excluded those who had not used the lotions for more than 10% of the time found and 80% reduction in *P. vivax* incidence in the treatment group. A reduction of 84% in *P. falciparum* incidence was also recorded in the treatment group, however this was not significant as case number were low (Hill *et al.* 2007).

### Study Rationale

Southeast Asian malaria vectors are known to bite outdoors in the evening as well as indoors during the night, meaning insecticide treated bed nets may only provide partial protection in these areas. It is hoped that repellents used during the evening could provide additional protection from malaria transmission over that given by treated bed nets. Following the encouraging results of a similar trial in Bolivia, this trial aims to establish whether Asian malaria vectors can also be prevented from transmitting malaria by the use of insect repellent.

### Potential Risks and Benefits

Finger-prick blood spots do cause modest, brief discomfort but are common in use in this area and it is likely most individuals will have already experienced this. Risk from this procedure is very low and antiseptic wipes are used to prevent infection.

Use of repellent is universal worldwide and present extremely low risk. We are using a high quality commercial brand made, registered and sold in the USA by SC Johnson. We are using the lowest effective dose of active 15% DEET and a consumer friendly gentle aqueous lotion formulation to minimise risk and discomfort. As young children have a lower body volume / skin surface ratio we will not enrol anyone under six years old. Full USA compliant consumer product information will be given verbally and in local language on the products. Any contraindications or side effects will be recorded and reported for appropriate action to local District Health departments. All positive cases will be referred for immediate treatment following local guidelines through the District Health teams working with us on the study. Treatment for *P. falciparum* with co-artem is free at the point of delivery in Lao PDR.

If findings are positive there would be a strong case for the use of repellents as part of future vector-borne disease control programmes.

## STUDY OBJECTIVES

### Objectives

The primary objective is to determine whether 15% DEET repellent used in the evening can reduce malaria incidence. Secondary objectives are to determine whether the intervention has an effect on fevers and dengue, Japanese Encephalitis (JE) and scrub typhus seroconversion. The trial will also monitor lotion acceptability and any occurrence of adverse events.

### Outcomes

The primary outcome measure will be the incidence of malaria defined as a positive rapid diagnostic test (RDT) result. Secondary outcomes will be all-cause fevers self reported via monthly questionnaires and seroconversion of dengue, JE and scrub typhus measured by ELISA test on dried bloodspots taken during baseline and exit surveys.

## METHODS

### Type of Study

A double-blind, randomised placebo-controlled trial of DEET repellent lotion used to prevent malaria transmission.

### Randomisation

Randomisation to repellent or placebo lotion will take place at the household level and is stratified by village. All the households in a village will be assigned to either group 258 or 305 (manufacturer codes of repellent and placebo lotions) during the baseline survey. District health workers who recruited and carried out the baseline survey labelled straws with the group codes which the heads of households then picked.

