### Blinding

The repellent and lotion were labelled by the manufacturers with a 3-digit code, and will reveal which is which at the end of trial. The trial staff and local health staff carrying out randomisation and surveys are therefore blinded to the treatment arms. Participants were informed as part of the recruitment process that they had an equal chance of receiving the placebo or repellent. The possibility does remain of participants being able to distinguish the DEET lotion from the placebo by a slight difference in smell.

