### Interventions

All participants will be provided with and sleep under long-lasting insecticide treated nets (LLINs) every night (PermaNet®2.0, deltamethrin 55mg/m2, mesh 25 holes/cm2). A 15% DEET lotion will be provided to half the households the other half of households will receive a placebo lotion (both supplied by SCJohnson). Adult participants will be provided with three 50ml bottles of their lotion to last one month (approximately 5ml per day). Children under 12 years will be provided with two bottles per month, corresponding to approximately 3ml per day. These exposures, based on Antwi *et al.* (2008), would have margins of exposure greater than 100 (exposure is less than 1% of NOEL) for acute and chronic toxicity. District health staff will demonstrate the amount of lotion to apply to arms and legs during the recruitment process. Participants are instructed to use the lotion every evening, but are free to also use the lotion during the day if desired.

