### Recruitment and Baseline Survey

Recruitment will take place in May 2009, when 300 households will be recruited from Attapeu province, and in April 2010, when 1,300 households will be recruited from both Attapeu and Sekong provinces. Participants will be recruited as volunteers from meetings with village members and local health team staff where the study will be described in full with opportunity for questions. Individuals that wish to take part will also receive this information in writing and sign a consent form to confirm they understand the trial, including the possibility they may receive the placebo lotion. A maximum of 25% of households will be recruited from any village in order to overcome diversion of bites to non-repellent users. In addition district health staff will be responsible for ensuring that study houses contain at least five eligible participants (if the household is bigger, more can be recruited), and that study houses are distributed throughout the village, the rule being that study houses should be a minimum of 10m apart. The baseline survey is scheduled for the same time as recruitment, May 2009 and April 2010. The questionnaire, estimated to take 30 minutes, will collect basic information on wealth indicators and current malaria prevention behaviour for the household and individual information on malaria exposure.

Households will be randomly assigned to one of the treatment groups and supplied with three 100ml bottles per person per month to allow for 10ml use per day as well as sufficient LLINs for the whole household, including non-participants (sufficient LLINs defined as one net for every 1.5 persons in the household, plus another for use away from home). District health staff will demonstrate how to use the lotion and explain that it should be used every evening. Participants will also be encouraged to use the lotion during the day if they notice biting.

A bloodspot will also be taken from each participant and stored on filter paper for laboratory analysis for dengue, JE and typhus. Analysis will ideally take place in Laos if facilities can be found, but if this is not possible the bloodspots will be transported to the UK or France for testing.

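### Recruiting staff also prepare and run the allocation draw, and nothing closes the household and member list first, so selection by arm is an unprotected risk

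*Protocol*

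**What the plan says.** The Randomisation section of the protocol sets the unit and the stratum: "Randomisation to repellent or placebo lotion will take place at the household level and is stratified by village". It then gives the codes and places the assignment within the baseline survey: "All the households in a village will be assigned to either group 258 or 305 (manufacturer codes of repellent and placebo lotions) during the baseline" […]. On who prepares the draw and who picks, it says: "District health workers who recruited and carried out the baseline survey labelled straws with the group codes which the heads of households then picked".

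The section Recruitment and Baseline Survey adds that "The baseline survey is scheduled for the same time as recruitment, May 2009 and April 2010". It gives the eligibility check to the same staff, and allows larger houses to enter with additional members: "district health staff will be responsible for ensuring that study houses contain at least five eligible participants (if the household is bigger, more can be" […]. They also see to the 10 m spacing between study houses. The Interventions section states the ratio: "A 15% DEET lotion will be provided to half the households the other half of households will receive a placebo lotion".

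Two statements in the Blinding section bear on the risk, one on each side. The manufacturer holds the meaning of the codes until the end of the trial, and "The trial staff and local health staff carrying out randomisation and surveys are therefore blinded to the treatment arms". But the section also grants that "The possibility does remain of participants being able to distinguish the DEET lotion from the placebo by a slight difference in smell".

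Finally, the section Participant and Household Withdrawal allows further recruitment in a village to be considered when a withdrawal falls in the first two months. It does not say how households recruited at that point are allocated.

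**The concern.** Concealment of allocation and blinding are separate protections. Blinding keeps the meaning of the code from staff after assignment. Concealment keeps the coming assignment from whoever decides on entry. The usual way to secure concealment is to let someone outside recruitment prepare the allocation, and to finish enrolment before it is revealed. The protocol does neither: one group of staff recruits, checks eligibility, labels the straws and runs the draw, and no step fixes who is in before the draw starts.

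This matters more in a household trial because two entry decisions are open: which households enter, and how many members beyond five are enrolled. Exposure differs between people, since the target population often works and sleeps away from the village. Malaria was also rare (0.7% incidence in the first year, by the Sample Size Calculation section), so modest differences in who is enrolled could weigh on the comparison.

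**Working it through.** The protocol states no figure on this point, so the check is mainly a reading of the sections together, followed by an illustration.

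**Is preparation of the allocation separate from enrolment?** No. Randomisation names the recruiting and surveying workers as those who label the straws. Recruitment and Baseline Survey gives the eligibility and spacing checks to district health staff and schedules baseline with recruitment. No independent preparer, list made in advance, hidden label or log of draws is described.

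**Is the roster closed before the draw?** No sentence requires it. The order of the text (meetings, consent, eligibility, questionnaire, then assignment) fits recruitment first, but does not make it a rule.

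**How could a code become an arm?** Four features in the protocol make this conceivable:
- There are only two codes, 258 and 305, so recognising one bottle reveals the arm of every household.
- A difference in smell is conceded for participants. Staff also handle the lotion, since they demonstrate its use during recruitment.
- Recruitment comes in two waves, 300 households in 2009 and 1,300 in 2010. No other codes are given for 2010, so an impression formed in the first season could carry into 1,300/1,600 = 81% of the households.
- Further recruitment after early withdrawals would take place when both codes are already in use in the village.

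**How predictable is the draw?** The protocol gives 1,600 households in 126 villages: 1,600/126 = 12.7 per village. Two cases follow, because it does not say whether straws are put back.

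1. *Assumption: equal numbers of each code, drawn one by one without replacement.* A person who always guesses the code with more straws left is expected to be right n/2 + 2^(n−1)/C(n, n/2) − 1/2 times in n draws.
   - n = 12: 6 + 2,048/924 − 0.5 = 7.716, and 7.716/12 = 64%.
   - n = 10: 6.532/10 = 65%. n = 14: 8.887/14 = 63%.
   - From n = 8 to n = 20 the share runs from 67% to 62%.
   - The last straw is always known. With m = n/2 = 6, the expected number of fully determined final draws is 2m/(m + 1) = 12/7 = 1.7.
2. *Assumption: straws are put back.* The guess is right 50% of the time and nothing is predictable. The number of households per arm in a village then has a standard deviation of √12.7/2 = 1.8, so an even split within villages is not ensured.

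**The case against.** The strongest reply is that the straws show a manufacturer's code, not a treatment. Staff are stated to be blinded, and the head of household picks, not the recruiter. Foreseeing a code is not foreseeing an arm. This stands, and it is why the point is a risk and not a finding of bias.

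The sequence is also open to a kinder reading. The workers are described as having recruited and surveyed, after which the heads of households picked, and assignment of all households in a village fits a single village draw. The shared timing is given by month, not by visit. Participants volunteer at village meetings, so staff do not choose households freely. The Study Schedule mentions SOPs, which may hold details of the draw. All this is fair, but it leaves the order to chance where one sentence would fix it.

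Three stronger readings are tempting and not supported:
- *That the allocation was openly visible.* The protocol does not say whether labels could be seen, so this would be an inference from silence.
- *That members were added after the draw.* The allowance for more than five members stands in the recruitment text, ahead of the sentence on assignment. Nothing permits later additions, although nothing forbids them.
- *That selection, had it occurred, would be beyond repair.* Wealth, prevention behaviour and individual exposure are recorded at baseline and the arms are compared on baseline data, so gross selection on measured factors could be seen and adjusted for. Selection on unmeasured factors would remain.

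The spread of 1.8 households per village under replacement is ordinary chance imbalance. Over 1,600 households the standard deviation is √1,600/2 = 20 around 800 per arm. It weakens the stratification by village but causes no bias.

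**Conclusion.** The point holds as an unprotected risk. The protocol puts recruitment, eligibility checks, labelling of straws and the draw in the same hands, and does not require the roster to be closed first. This is a procedure that the protocol itself fixes, and a better one is readily available.

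A reader might infer that households or members were in fact selected by arm. The documents do not show this. It would need the code to be recognised or suspected and, in addition, entry decisions still open when the next code is known or guessable. The 64% is the chance of guessing a code, not an arm, and it measures no bias. It rests on equal numbers of straws, no replacement and one-by-one draws, and it matters only if enrolment is interleaved with the draws. None of these is stated. No sample size figure changes.

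**What to change.** Amend the Randomisation section and the recruitment text as follows:
- In each village, complete consent, eligibility, member list and baseline questionnaire for all study households, and close the roster before any draw.
- Have the project office, not the recruiting staff, prepare a concealed 1:1 allocation per village, as sealed numbered envelopes or straws with hidden labels. This also settles whether straws are put back.
- Log each draw against the closed roster.
- Allow no members to be added to a household after allocation.
- Allocate any households recruited after early withdrawals from the same concealed list.

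The version at hand already uses first-year results, so the 2009 draws can only be documented: whether labels were hidden, whether straws were put back, and whether rosters were complete. Comparing the number of enrolled members per household and the recorded exposure between the two codes would be a useful check.

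The cost is a little preparation for each of the 126 villages, and lotion is handed out only once the roster is closed.
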